### Sample size calculation

2.10

The sample size was calculated based on the co-primary outcomes: response rates for functional disability and self-reported back pain bothersomeness. The primary outcome is defined as the proportion of patients achieving clinically meaningful improvement, defined as at least a 30% improvement from baseline, in both functional disability and back pain bothersomeness after 8 weeks of intervention. Based on previous studies of mind-body interventions for chronic low back pain (15, 39), we assumed that 35% of participants in the usual care group and 55% of participants in the VR-MBCT group would achieve clinically meaningful improvement, corresponding to an absolute between-group difference of 20 percentage points. With a two-sided significance level of 0.05, 80% power, and a 1:1 allocation ratio, 97 patients per group were required for each co-primary outcome. This sample size was considered sufficient to provide adequate power for both co-primary outcomes; the study will be considered positive only if both outcomes reach statistical significance. Allowing for a 10% dropout rate, the total sample size was set at 214 patients, with 107 patients in each group. Sample size calculations were performed using PASS software, version 15.0 (NCSS, LLC, USA).

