### Statistical analysis

2.11

All analyses will follow a prespecified statistical analysis plan and will be conducted according to the intention-to-treat principle, whereby participants will be analyzed according to their randomized group assignment regardless of intervention adherence. Continuous variables will be summarized as means with standard deviations or medians with interquartile ranges, as appropriate, while categorical variables will be summarized as frequencies and percentages. All statistical tests will be two-sided, and statistical significance will be defined as a *P* value <0.05.

For the co-primary outcomes, separate regression models will be fitted for functional disability and self-reported back pain bothersomeness. Outcomes from all follow-up time points (weeks 4, 8, and 26) will be analyzed simultaneously using generalized estimating equations (GEEs) to account for within-participant correlations over time. Because treatment effects may vary across follow-up periods, models will include fixed effects for treatment group, time point, and treatment-by-time interaction terms. Baseline values of the corresponding outcome measures, study center, age group (≥60 years vs. <60 years), sex, pain duration, and other clinically relevant baseline covariates associated with outcomes or missingness will be included as adjustment variables.

The co-primary outcomes are binary responder outcomes, defined as at least a 30% improvement from baseline. Therefore, modified Poisson regression models with a log-link function and robust sandwich variance estimators will be used within the GEE framework to estimate relative risks and corresponding 95% confidence intervals. The primary endpoint will be evaluated at week 8. The study will be considered positive only if both co-primary outcomes reach statistical significance at the primary endpoint.

Continuous secondary outcomes, including pain intensity, psychological scores, sleep quality, physical activity, fear-avoidance beliefs, pain catastrophizing, and work productivity, will be analyzed using linear GEE models or linear mixed-effects models, as appropriate according to outcome distributions and covariance structures. Secondary outcomes assessed only at selected time points will be analyzed using models including the corresponding follow-up assessments.

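### 97 per group gives about 80% power for each co-primary outcome but only about 65–73% for the rule that both must be significant, so the adequacy claim is unsupported

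*Protocol article*

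**What the plan says.** Sample size calculation (2.10) takes one pair of response rates: "we assumed that 35% of participants in the usual care group and 55% of participants in the VR-MBCT group would achieve clinically meaningful improvement". The design parameters follow: "With a two-sided significance level of 0.05, 80% power, and a 1:1 allocation ratio". The result is stated per outcome: "97 patients per group were required for each co-primary outcome". The next sentence draws the conclusion at issue, "This sample size was considered sufficient to provide adequate power for both co-primary outcomes", and continues, "the study will be considered positive only if both outcomes reach statistical significance". The section then arrives at the enrolment target: "Allowing for a 10% dropout rate, the total sample size was set at 214 patients, with 107 patients in each group".

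Statistical analysis (2.11) fits one model for disability and another for bothersomeness, and repeats the rule: "The study will be considered positive only if both co-primary outcomes reach statistical significance at the primary endpoint".

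Three places describe the endpoint differently. Primary outcome (2.4) calls it both co-primary and composite, and asks for improvement on the two measures together. Sample size calculation (2.10) and the Discussion (3) also define response as a gain of at least 30% on both measures. No section states a correlation between the outcomes or a power for the two tests jointly.

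**The concern.** The 80% belongs to one test, while the success rule is the intersection of two. Requiring both tests to be significant needs no correction of the significance level, but it costs power, because the trial fails if either test misses. That loss does not appear in the calculation, yet the sample size is called adequate for both outcomes. The only power target in the protocol is 80%, so that is the standard for judging the word adequate.

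At stake is how a non-positive trial is read. A reader of the sample size section would suppose that a true 20-point benefit on both outcomes would be missed about one time in five. Under the trial's own rule the chance of missing it is higher.

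**Working it through.** **Inputs.** From Sample size calculation (2.10): 35% versus 55%, two-sided 0.05, 80% power, 1:1 allocation, 97 per group for each co-primary outcome, 107 per group enrolled. From 2.10 and Statistical analysis (2.11): separate tests, both of which must be significant. Assumed here: the 35% and 55% hold for each outcome, and the two test statistics have correlation ρ. The documents do not give ρ, so it is varied.

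**Step 1: reproduce the plan's figure.** Pooled two-proportion formula with mean rate 0.45:

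n = [1.96·√(2·0.45·0.55) + 0.8416·√(0.35·0.65 + 0.55·0.45)]² / 0.20²
= [1.96·√0.495 + 0.8416·√0.475]² / 0.04 = 95.9, so 96 per group.

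The stated 97 agrees to within one patient. It is a single-outcome number.

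**Step 2: power of one test at 97 per group.**

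b = (0.20·√97 − 1.96·√0.495) / √0.475 = (1.970 − 1.379) / 0.689 = 0.857, and Φ(0.857) = 0.804.

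Each test therefore has 80.4% power, as the protocol says.

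**Step 3: power of the success rule.** The probability that both tests are significant is Φ₂(b, b; ρ), the bivariate normal probability with correlation ρ. At ρ = 0 it is 0.804² = 0.647.

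| Assumed ρ | Both significant, 97 per group | Simulation, 97 per group | Both significant, 107 per group (no dropout) |
|---|---|---|---|
| 0 | 64.7% | 65.2% | 70.8% |
| 0.3 | 67.3% | 67.9% | 72.9% |
| 0.5 | 69.3% | 69.7% | 74.6% |
| 0.7 | 71.9% | 72.4% | 76.7% |
| 0.8 | 73.4% | 73.9% | 78.1% |
| 0.9 | 75.5% | 75.9% | 79.9% |

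The simulation drew correlated binary outcomes (200,000 runs per row, with ρ as the within-patient correlation of the two responses) and applied the same pooled test to each. At 97 per group, joint power returns to 80.4% only at ρ = 1; at ρ = 0.95 it is 77.0%.

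**Step 4: what this means for a true effect.** For ρ from 0 to 0.8, the chance of missing a true 20-point difference on both outcomes is 100 − 73.4 = 26.6% to 100 − 64.7 = 35.3%, against the 20% implied by the stated power.

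**The case against.** The strongest reply is that the endpoint is a single composite responder. Sections 2.4, 2.10 and 3 all define response as improvement on both measures, and in 2.10 that definition stands directly before the 35% and 55%. If those rates describe the composite and one test is made of it, 97 per group has about 80% power. The component rates would then be at least as high and are not given, so the 65–73% would not follow. This exposes a real conflict in the text, but it does not rescue the sentence. The 97 is stated per co-primary outcome, the models are separate, both must be significant, and no analysis of a composite variable is described.

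It can also be said that the protocol never claims 80% joint power and that adequate is a loose word. That stands in part. A reader might infer that the 80% was miscalculated, and it was not: it is correct and is labelled as the power for each outcome. The fault is the claim built on it.

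The planned analysis is a covariate-adjusted modified Poisson GEE, not a simple comparison of proportions. Adjustment may change power, but 2.10 relies on no such gain. An unadjusted Wald test of the log relative risk at 97 per group has 77.7% power per outcome, slightly less than the figure used here.

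A reader might further infer a dropout error, since 97/0.9 = 107.8 would round to 108, whereas 97 × 1.10 = 106.7 gives the stated 107. This is a rounding convention worth one patient per group: 107 × 0.9 = 96.3, and 96 already gives 80.0% power per test. It needs no correction.

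**Conclusion.** The concern holds as a missing joint-power statement. Power is about 80% for each co-primary outcome. For the condition that defines a positive trial it is about 65% to 73% at 97 evaluable per group, for assumed correlations of 0 to 0.8, and about 75% at 0.9. Against the protocol's own 80% target the shortfall is about 7 to 15 points over the 0 to 0.8 range. Full retention of 107 per group narrows the gap but leaves joint power below 80% across the correlations tabulated, only marginally so at 0.9.

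These figures assume that the 35% and 55% apply to each outcome and that the test is unadjusted. A single value such as 69% should not be quoted as the trial's power, because it would adopt a correlation of 0.5 that the documents do not supply.

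A reader might also infer that the two tests inflate the type I error or that the trial must enrol more patients. Neither follows. Using the full 0.05 for each test is right when both must be significant, and a trial may proceed with lower joint power provided that it says so.

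**What to change.** In Sample size calculation (2.10), replace the adequacy statement with:

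> 97 per group gives about 80% power for each co-primary outcome; power for both to be significant, the condition for a positive trial, is about 65–73% for assumed correlations of 0 to 0.8.

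Then reconcile the single responder definition in 2.4, 2.10 and the Discussion (3) with the two separately tested outcomes in 2.10 and 2.11, and state which of them the 35% and 55% describe. The replacement sentence is valid if the rates apply to each outcome. If they describe the composite, the rates for each component have to be stated before any joint power can be given.

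The cost is a few sentences, repeated wherever the analysis plan restates the sample size, and a less favourable power figure in print. Enrolment, tests, significance level and success rule all stay as they are, and the dropout sentence can stand.

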### Statistical analysis

2.11

All analyses will follow a prespecified statistical analysis plan and will be conducted according to the intention-to-treat principle, whereby participants will be analyzed according to their randomized group assignment regardless of intervention adherence. Continuous variables will be summarized as means with standard deviations or medians with interquartile ranges, as appropriate, while categorical variables will be summarized as frequencies and percentages. All statistical tests will be two-sided, and statistical significance will be defined as a *P* value <0.05.

For the co-primary outcomes, separate regression models will be fitted for functional disability and self-reported back pain bothersomeness. Outcomes from all follow-up time points (weeks 4, 8, and 26) will be analyzed simultaneously using generalized estimating equations (GEEs) to account for within-participant correlations over time. Because treatment effects may vary across follow-up periods, models will include fixed effects for treatment group, time point, and treatment-by-time interaction terms. Baseline values of the corresponding outcome measures, study center, age group (≥60 years vs. <60 years), sex, pain duration, and other clinically relevant baseline covariates associated with outcomes or missingness will be included as adjustment variables.

The co-primary outcomes are binary responder outcomes, defined as at least a 30% improvement from baseline. Therefore, modified Poisson regression models with a log-link function and robust sandwich variance estimators will be used within the GEE framework to estimate relative risks and corresponding 95% confidence intervals. The primary endpoint will be evaluated at week 8. The study will be considered positive only if both co-primary outcomes reach statistical significance at the primary endpoint.

Continuous secondary outcomes, including pain intensity, psychological scores, sleep quality, physical activity, fear-avoidance beliefs, pain catastrophizing, and work productivity, will be analyzed using linear GEE models or linear mixed-effects models, as appropriate according to outcome distributions and covariance structures. Secondary outcomes assessed only at selected time points will be analyzed using models including the corresponding follow-up assessments.

Missing outcome data will initially be handled under a missing-at-random assumption using likelihood-based estimation within the GEE framework and adjustment for predictors of missingness. Sensitivity analyses will be performed using multiple imputation methods and per-protocol analyses to evaluate the robustness of the findings under different missing-data assumptions.

Safety analyses will include all participants who received at least one intervention session. Adverse events will be summarized descriptively and compared between groups using chi-square tests or Fisher exact tests, as appropriate.

All analyses will be performed using R software (R Foundation for Statistical Computing, Vienna, Austria) or SPSS software (IBM Corp., Armonk, NY, USA).

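### The protocol claims likelihood-based handling of missing co-primary outcomes, but the planned modified Poisson GEE has no likelihood and does not reliably cover dropout that depends on week-4 response

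*Protocol article*

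**What the plan says.** Protocol article, section 2.11 (Statistical analysis), on missing data: "Missing outcome data will initially be handled under a missing-at-random assumption using likelihood-based estimation within the GEE framework", followed by "and adjustment for predictors of missingness".

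The co-primary model is fixed in the same section: "modified Poisson regression models with a log-link function and robust sandwich variance estimators will be used within the GEE framework". Weeks 4, 8 and 26 enter one model with group, time and group-by-time terms, and "The primary endpoint will be evaluated at week 8". The adjustment set is the baseline value of the outcome, centre, age group, sex and pain duration, and it closes with "other clinically relevant baseline covariates associated with outcomes or missingness will be included as adjustment variables". The section names no weighting or imputation for the primary analysis and no working correlation.

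As a check: "Sensitivity analyses will be performed using multiple imputation methods and per-protocol analyses". Continuous secondary outcomes "will be analyzed using linear GEE models or linear mixed-effects models, as appropriate according to outcome distributions and covariance structures".

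**The concern.** Dropout that is missing at random can be ignored in a full likelihood analysis because the likelihood uses each participant's earlier outcomes to inform the missing ones. GEE has no likelihood, so it does not inherit that property. A Poisson working model for a yes/no response is not the likelihood of the data either, which is why the sandwich variance is needed. The sandwich repairs standard errors. It does not repair a point estimate distorted by who stayed in.

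Adjustment for baseline predictors covers missingness that depends on those predictors. It does not cover a participant who leaves after week 4 because of the week-4 result. That is ordinary missing-at-random dropout, and the week-4 outcome is in the dataset.

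The stake is the week-8 relative risk for each co-primary outcome, because both must be significant for the trial to be called positive. Participants know their allocation (section 2.7), and only the VR-MBCT arm has weekly clinic sessions and home practice (section 2.8), so reasons for leaving could differ by arm.

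**Working it through.** **The plan's own figures (section 2.10).** Response of 55% against 35% gives RR = 0.55/0.35 = 1.571. The pooled two-proportion formula gives 96 per group, against the stated 97; power at 97 is 80.4%. Planned dropout is 10%, and 107 × 0.9 = 96.3. So 10% dropout is the benchmark below.

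**Formula.** With group-by-time terms, an independence working correlation and no covariates, the GEE week-8 rate in an arm is the observed-case proportion. Let p4 and p8 be the response rates at weeks 4 and 8. Let a and b be the chance of week-8 response given week-4 response and non-response. Let k1 and k0 be the shares of all randomised participants lost after week 4 from those two groups.

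- b = (p8 − p4·a)/(1 − p4)
- observed rate = [(p4 − k1)·a + (1 − p4 − k0)·b]/(1 − k1 − k0)

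**First set of assumed inputs** (not in the document): p4 = 0.45 VR-MBCT and 0.28 usual care; a = 0.85 and 0.75.

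- VR-MBCT: b = (0.55 − 0.3825)/0.55 = 0.3045
- Usual care: b = (0.35 − 0.21)/0.72 = 0.1944
- VR-MBCT, 10% lost, all week-4 non-responders: (0.3825 + 0.45 × 0.3045)/0.90 = 0.577
- Usual care, 10% lost at random: 0.350
- Usual care, 10% lost, all week-4 responders: (0.18 × 0.75 + 0.14)/0.90 = 0.306
- Usual care, 10% lost, all week-4 non-responders: (0.21 + 0.62 × 0.1944)/0.90 = 0.367

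| Pattern at 10% per arm | RR | Bias against 1.571 |
|---|---|---|
| VR-MBCT loses non-responders, usual care random | 0.577/0.350 = 1.65 | +5% |
| Opposite directions | 0.577/0.306 = 1.89 | +20% |
| Non-responders lost in both arms | 0.577/0.367 = 1.57 | 0% |

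Standardising over week-4 response, which uses the week-4 data, recovers the truth. For VR-MBCT: 0.45 × 0.85 + 0.55 × 0.3045 = 0.55.

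**Second set of assumed inputs:** week-4 response 40% and 25%, latent correlation between visits 0.5 to 0.7, and dropout only partly concentrated by week-4 response.

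- About 10% VR-MBCT dropout, mostly non-responders; usual care random: RR 1.61 to 1.63, +2% to +3.5%
- 20% VR-MBCT dropout, usual care 10% random: RR 1.64 to 1.68, +5% to +7%
- About 10% per arm in opposite directions: RR 1.70 to 1.77, +8% to +13%
- Same mechanism in both arms: −0.5% to −0.8%

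With no true effect and 107 randomised per arm, the two-sided type I error per outcome is 0.052 to 0.056 at about 12% VR-MBCT dropout. With opposite directions it is 0.072 to 0.099.

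**Working correlation.** In a simulation of 20,000 per arm with about 20% VR-MBCT dropout, the week-8 RR was 1.537 on full data. Independence GEE gave 1.639 (1.639/1.537, about +7%), exchangeable GEE 1.522 (about −1%), and the estimator standardised over week-4 response 1.538.

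**The case against.** The strongest reply is that one phrase is wrong and little follows from it. Baseline adjustment deals with part of the missingness. Multiple imputation is already prespecified and, if it uses week-4 data, would expose the bias. The larger figures rest on an independence working correlation, which the article does not state. Section 2.11 says GEE is chosen to account for correlation within participants, which points the other way, and the structure can properly be left to the analysis plan. In simulations of the first set of inputs (with an added assumption for week 26), exchangeable GEE gave about 1.59 with 10% VR-MBCT dropout, 1.55 with 20%, and 1.51 with opposite directions, against a true 1.57.

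Much of this stands, and it limits the expected size. It does not make the sentence true. Protection from an exchangeable structure depends on how close that structure is to the truth.

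Three stronger readings are tempting but unsupported:

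- A reader might infer that dropout will be response-related and differ by arm, so that relative risks near 1.9 are to be expected. Open-label conduct makes this possible, but the document gives no dropout pattern. The offer of the programme to controls after follow-up may help retain them.
- A reader might infer that the week-8 estimate is simply a complete-case analysis. That is exact only for the unadjusted independence model. With covariate coefficients shared across visits, the other weeks contribute.
- A reader might infer that fixing a linear mixed model would cure the same problem for continuous secondary outcomes. Section 2.5 schedules these at baseline, week 8 and week 26 unless otherwise stated, and lists only satisfaction at week 4. A mixed model for them has no week-4 value to use.

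**Conclusion.** The point holds as a wrong statement about the co-primary analysis, with a consequence that can matter but need not. The plan claims a missing-at-random property that the specified estimator lacks, and baseline-only adjustment leaves dropout driven by week-4 response not reliably covered.

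At the planned 10% dropout, the bias in the week-8 relative risk is about +2% to +5% if only VR-MBCT dropout is response-related. It is about +8% to +20% if the arms lose participants in opposite directions, and 0% to −1% if they share the mechanism. These ranges rest on assumed week-4 rates, visit-to-visit dependence and dropout patterns, on an independence working correlation, and on an unadjusted model. With a well-chosen exchangeable structure the bias is much smaller and not consistently upward.

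This should be corrected before outcome data are analysed. Because multiple imputation is already planned and the bias is small in the milder cases, it is not a flaw that invalidates the design.

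**What to change.** 1. In section 2.11, delete the claim of likelihood-based estimation within GEE.
2. Promote the planned multiple imputation to the primary co-primary analysis. Impute the ODI and bothersomeness scores separately by arm, from baseline values, week-4 and other follow-up scores, the stratification factors and, in the VR-MBCT arm, session attendance. Then derive the 30% response, fit the same modified Poisson GEE to each completed dataset and combine the results by Rubin's rules.
3. Inverse-probability-weighted GEE, with weights that use week-4 data, is an acceptable alternative.
4. Keep the unweighted GEE as a sensitivity analysis.

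The cost is a change of wording and modest programming. Week-4 outcomes (section 2.11) and attendance (Discussion) are already to be recorded. The downside is that the primary result then relies on an imputation or weighting model, which has to be specified in advance.

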### Safety outcomes

2.6

Adverse events will be monitored at each participant contact. VR-related symptoms, including dizziness, nausea and vomiting, headache, eye soreness, and falls, will be recorded. These symptoms are expected to be mostly mild and transient. If a participant experiences a fall or significant discomfort, the intervention session will be paused or discontinued as appropriate. Serious adverse events will be reported to the Data and Safety Monitoring Committee within 24 h.

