Participants assigned to the intervention group will attend one facilitator-guided, in-clinic VR-MBCT session per week for 8 weeks, with each session lasting approximately 30 min. Between sessions, they will complete audio-guided mindfulness practice at home three times per week, with each practice lasting 20–30 min. No VR equipment will be used for home practice. Each in-clinic session will be automatically generated by the system and facilitated by trained research staff, who will assist with equipment setup, safety monitoring, and procedural guidance. The 8-week progressive curriculum is summarized in Supplementary Table S1 and includes the following themes: automatic pilot and awareness, including body scan and mindful breathing; body scan and movement repertoire, including cat-cow exercises and visual feedback; mindful movement and graded exposure, including system-adjusted spinal and core exercises; responding rather than reacting, including the ABC model and urge surfing; cognitive defusion, including thought replacement exercises; self-compassion, including acceptance narratives and posture transitions; relapse prevention and self-care, including compassionate letter writing and loving-kindness meditation; and maintenance planning and real-world transfer, including system- guided training and individualized maintenance planning. A detailed breakdown of weekly themes, VR core scenes, and key teaching points is provided in Supplementary Table S1.

System-generated data will include training duration, module completion, and pause events. Self-reported data, including ABC practice logs and scene preferences, as well as anxiety scores assessed using a 0–10 visual analogue scale before and after each VR session, will be collected through the system interface. Research staff will conduct weekly telephone follow-ups to promote participant adherence. If a participant misses a VR session, a brief motivational interview will be conducted to identify barriers and encourage continued participation.

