Participants in the control group will receive standard clinical care, including pharmacological treatment, such as analgesics, and physical therapy, such as extracorporeal shock wave therapy. They will not receive structured VR training during the initial 8-week study period. After completing the 6-month follow-up assessment, participants in the control group may receive the same 8-week VR-MBCT program according to their preferences. Group allocation will remain concealed from outcome assessors and statisticians until study completion.

Randomization will be conducted before the study begins by an independent researcher using a computer-generated randomization sequence with stratified block randomization according to study center and age (≥60 years or <60 years), using block sizes of 2 and 4. Group assignments will be concealed using sequentially numbered, sealed, opaque envelopes, which will only be opened after the participant is enrolled and assigned. Due to the nature of the VR-based intervention, blinding of participants and intervention therapists is not feasible. However, outcome assessors and statisticians will remain blinded to group allocation throughout the study to minimize detection bias. The schedule for patient enrollment, study interventions, and outcome assessments will adhere to the SPIRIT statement (Supplementary Table S2).

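### The safety set is defined by receipt of an intervention session, which no usual-care participant can meet through week 26, so the planned between-arm adverse event comparison has no comparator

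*Protocol article*

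**What the plan says.** All references are to the protocol article.

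- **Safety population (section 2.11).** "Safety analyses will include all participants who received at least one intervention session".
- **Planned comparison (section 2.11, next sentence).** "Adverse events will be summarized descriptively and compared between groups using chi-square tests or Fisher exact tests, as appropriate".
- **Who has sessions (section 2.8).** "Participants assigned to the intervention group will attend one facilitator-guided, in-clinic VR-MBCT session per week for 8 weeks". No session of any kind is described for the other arm.
- **What controls receive (section 2.8).** "Participants in the control group will receive standard clinical care, including pharmacological treatment, such as analgesics, and physical therapy". Of VR the section says: "They will not receive structured VR training during the initial 8-week study period".
- **When controls may have VR-MBCT (section 2.8).** "After completing the 6-month follow-up assessment, participants in the control group may receive the same 8-week VR-MBCT program according to their preferences".
- **How events are collected (section 2.6).** "Adverse events will be monitored at each participant contact". This is not limited to one arm.

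Section 2.11 also opens with a general intention-to-treat statement. No section gives a separate safety-set rule for usual care.

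**The concern.** The two adjacent safety sentences in section 2.11 do not fit together. The first admits participants by exposure to a treatment that only one arm receives. The second needs both arms. An analyst who applies the first sentence has nobody in usual care to compare with.

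Safety is a stated aim of the trial. The events of interest (dizziness, headache, nausea and vomiting, falls) also occur in patients who never wear a headset, so a rate from the VR-MBCT arm alone cannot show an excess. If the rule is mended only once the data have been seen, the choice of who counts is made after the fact.

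**Working it through.** **Inputs.** There are 107 participants per arm, 214 in total (section 2.10; 2 × 107 = 214). The population rule and the tests come from section 2.11, and treatment exposure by arm from section 2.8. The plan states no safety-set size and no adverse event rate, so there is no safety figure to reproduce. The event counts in steps 3 and 4 are assumptions for illustration.

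**Step 1: who meets the rule.**

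- VR-MBCT: everyone who starts one or more of the 8 weekly sessions, so at most 107.
- Usual care, weeks 0 to 8: VR is expressly excluded, so 0.
- Usual care, weeks 8 to 26: the exclusion sentence covers only the first 8 weeks, but the next one places the VR-MBCT offer after the 6-month assessment. By inference, 0.

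The safety table through week 26 is therefore up to 107 versus 0.

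**Step 2: do other readings supply a comparator?**

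- A session could be taken to include a usual-care visit. Section 2.8 describes no such sessions and sets the intervention group against the control group.
- The general intention-to-treat statement could be taken to govern. It covers all analyses, but the safety sentence then sets its own, narrower exposure criterion. That leaves one more statement to reconcile.

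**Step 3: can the stated tests run on 107 versus 0?** Assume 10 of 107 VR-MBCT participants have an event.

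- Chi-square: expected count = row total × column total / N. For usual care this is 0 × 10 / 107 = 0, so the statistic cannot be computed.
- Fisher exact: the odds ratio is undefined and p = 1.0, because an empty row carries no information.

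**Step 4: the same tests with usual care restored (107 versus 107).** VR-MBCT is held at 10/107 = 9.3%.

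| Usual-care events (assumed) | Usual-care rate | Difference | Odds ratio | Fisher p |
|---|---|---|---|---|
| 0 | 0% | 9.3 points | infinite | 0.0016 |
| 3 | 2.8% | 6.5 points | 3.57 | 0.082 |
| 5 | 4.7% | 4.7 points | 2.10 | 0.28 |
| 10 | 9.3% | 0 points | 1.00 | 1.0 |

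The same VR-MBCT count can look like a clear excess or none at all, depending entirely on the usual-care count that the written rule leaves out.

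**Step 5: is ascertainment equal once controls are included?** Section 2.9 describes follow-up at weeks 4, 8 and 26, which gives 3 contacts. Section 2.8 adds 8 weekly sessions and weekly telephone calls in the VR-MBCT arm. Assume that the calls are for that arm only (they appear in the intervention description and serve adherence), that they run for the 8 weeks, and that no contacts coincide. That arm then has up to 3 + 8 + 8 = 19 contacts against 3. Since events are recorded at each contact, a raw excess could partly reflect how often people were asked.

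**The case against.** The strongest reply is that the intent is easy to infer. The next sentence compares the arms, so the session rule was presumably meant for VR-MBCT participants, with usual care as the comparator. The analysis is not primary. Events are monitored without restriction by arm, so the text can be corrected at any time before analysis. An unseen analysis plan may also define the sets properly.

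Most of this stands and limits the severity. It does not remove the error. The article does not leave the safety population to another document. It states one, and that one conflicts with the stated test. An analysis plan that followed the sentence would inherit the problem, and one that did not would contradict the published protocol.

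Two stronger readings are tempting, and the document supports neither.

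- A reader might infer that controls who take VR-MBCT after week 26 would become the comparison group. They would meet the session rule literally. However, week 26 is the last scheduled assessment, no adverse event collection is described for the later offer, and section 2.1 ends follow-up in January 2027. Nothing suggests that those events would enter the comparison.
- A reader might infer that control-arm safety data will not exist. Section 2.6 points the other way.

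A further objection also stands: adding the controls makes the test computable but not automatically interpretable, because contact frequency differs between the arms. The fix has to deal with that.

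**Conclusion.** The point holds as an internal contradiction in section 2.11. Through week 26 the stated safety set contains up to 107 VR-MBCT participants and 0 usual-care participants, and the planned between-arm comparison cannot be made on it. With usual care included it would be up to 107 versus 107.

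This rests on two readings: that a session means a VR-MBCT session, the only kind described, and that controls have no VR-MBCT before the 6-month assessment. The 0 is a count of who qualifies under the rule. It is not a measured effect on any result.

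Severity is moderate. A reader might take the point as a threat to the trial's main conclusion, and it is not one: the primary efficacy analysis and the sample size do not use the safety set. Analysis by treatment received, a restricted list of compared events, or a particular interval method would be reporting choices. Resolving the contradiction does not require them.

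**What to change.** Reword the safety paragraph of section 2.11, and the analysis plan to match:

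1. The safety set is all randomised usual-care participants plus VR-MBCT participants who started one or more sessions. Report how many VR-MBCT participants never started.
2. Adverse events are counted over the same window in both arms, from randomisation to week 26.
3. The between-arm comparison uses events elicited at the shared week 4, 8 and 26 contacts, with the same question in both arms covering the time since the previous shared contact (or since randomisation, at week 4).
4. Events noted only at VR sessions or weekly calls are listed descriptively for the VR-MBCT arm and kept out of the test.

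The cost is one paragraph of text, settled before any data are analysed. No added visits or participants are needed. Item 3 needs a common adverse event question at three contacts that already exist, and the case report form should be checked for it. Item 4 needs the form to record the contact at which each event was noted.
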